### 6.1.2 Treatment Phase Procedures

The following assessments should be performed on Day 1 of each cycle before administering drug unless otherwise noted. Please refer to [Appendix 4](#) for details of response evaluation to be completed at any time throughout the trial when a CR or better is suspected.

|                                                                                                                                                                                   |                                                                                                                                                                                                                                                                                                                                                                                                                                                |
|-----------------------------------------------------------------------------------------------------------------------------------------------------------------------------------|------------------------------------------------------------------------------------------------------------------------------------------------------------------------------------------------------------------------------------------------------------------------------------------------------------------------------------------------------------------------------------------------------------------------------------------------|
| Complete Physical Examination and Vital Signs on Day 1
Symptom-directed Physical Exam Days 8 and 15
Vital Signs on each treatment day with carfilzomib | 
 
• Body weight
 
• BSA
 
• ECOG Performance Status
 
• Blood pressure, pulse, temperature
 
• Pulse oximetry to investigator discretion
 
                                                                                                                                                                                                                           |
| Hematology
Days 1, 8, and 15 before carfilzomib administration                                                                                                          | Hemoglobin, hematocrit, WBC count; WBC differential, red blood cell count, platelets. WBC differential may be automated or manual as per institutional standards.                                                                                                                                                                                                                                                                              |
| Complete Clinical Chemistry
Days 1, 8, and 15 before carfilzomib administration                                                                                         | Sodium, potassium, chloride, bicarbonate, BUN, creatinine, glucose, uric acid, total protein, albumin, calcium, phosphorus, magnesium, total bilirubin, alkaline phosphatase, ALT, AST, LDH. Results must be reviewed before dosing in Cycles 1 and 2.                                                                                                                                                                                         |
| Limited Clinical Chemistry
Days 2, 9, and 16 if clinically indicated                                                                                                    | Sodium, chloride, bicarbonate, BUN, creatinine, glucose, uric acid                                                                                                                                                                                                                                                                                                                                                                             |
| Pregnancy Test                                                                                                                                                             | FCBP with regular or no menstrual cycles must agree to have pregnancy tests every 7 days (weekly) for the first 28 days of study participation and then every 28 days while on study. If menstrual cycles are irregular, the pregnancy testing must occur weekly for the first 28 days and then every 14 days while on study.                                                                                                                  |
| Myeloma Disease Assessment Laboratory                                                                                                                                      | M-protein determination: 
 
• Serum protein electrophoresis and immunofixation
 
• Urine protein electrophoresis and immunofixation
 
• Serum free light chains and Hevylite test
 
• Serum quantitative immunoglobulins
 
 Only those assessments used to follow the myeloma disease are required past screening. All assessments are required for confirmation of response. |
| Aspirate/Biopsy                                                                                                                                                            | All BM aspirates are SOC. Quantify percent myeloma cell involvement, and obtain bone marrow aspirate for MRD analysis by NGS. This is required at end of Cycle 8, 24 and confirmation of CR. If a CR is suspected after Cycle 8, a bone marrow biopsy and MRD testing will be completed at Cycle 12 to confirm. For subjects who sign consent for correlative                                                                                  |

|                                 |                                                                                                                               |
|---------------------------------|-------------------------------------------------------------------------------------------------------------------------------|
|                                 | samples, an additional aspirate sample should be collected at the time of the SOC BMA.                                        |
| CT-PET                   | A CT-PET must be performed to confirm MRD-negative disease per standard of care (SOC), at every timepoint when MRD is checked |
| Neurotoxicity Assessment | Including Neurotoxicity Questionnaire ( Appendix 5 )                                                          |
| QOL Assessment           | Patient reported survey ( Appendix 6 )                                                                        |
| Adverse Events           | Assessed on an ongoing basis                                                                                                  |
| Study Treatment          | Section 7 and Appendix 8 (Schedule of Events)                                                 |

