### **6.3 Study Drug Administration**

#### **6.3.1 Carfilzomib Administration**

Carfilzomib for injection is supplied as a lyophilized parenteral product in single-use vials. The lyophilized product is reconstituted with water for injection to a final carfilzomib concentration of 2.0 mg/mL prior to administration. The dose will be calculated using the subject's actual BSA at baseline. Subjects with a BSA  $> 2.2 \text{ m}^2$  will receive a dose based upon a  $2.2 \text{ m}^2$  BSA. Dose adjustments do not need to be made for weight gains/losses of  $\leq 10\%$ . Subjects with a Body Surface Area (BSA) of greater than  $2.2 \text{ m}^2$  will receive a capped dose of 44 mg of carfilzomib (at the  $20 \text{ mg/m}^2$  dose level), 59.4 mg of carfilzomib (at the  $27 \text{ mg/m}^2$  dose level), or 79.2 (at the  $36 \text{ mg/m}^2$  dose level).

Carfilzomib will be given as an IV infusion over 30 minutes on Days 1, 2, 8, 9, 15 and 16 of Cycles 1- 8 and Days 1, 2, 15 and 16 of Cycles 9-24, and must be administered prior to daratumumab. If the subject has a dedicated line for carfilzomib administration, the line must be flushed with a minimum of 20 mL of normal saline prior to and after drug administration. The dose will be administered at a facility capable of managing hypersensitivity reactions. Subjects will be pre-hydrated with 250mL normal saline or other appropriate IV fluid formulation on cycle 1 Day 1. Other hydration procedures will be optional and per the discretion of the treating investigator. Subjects will remain at the clinic under observation for at least 1 hour following each dose of carfilzomib in Cycle 1 and following the dose on Cycle 2, Day 1. Subjects should be monitored periodically during this period for evidence of fluid overload. Serum chemistry values, including creatinine, must be obtained and reviewed prior to each dose of carfilzomib during Cycles 1 and 2. Refer to [Table 6-8](#) for guidance regarding dose reduction in subjects with compromised renal function.

Doses of carfilzomib may be rescheduled up to 2 days if the scheduled day falls upon a holiday or with approval from the Lead Principal Investigator. If Day 2 of Carfilzomib dosing is delayed (i.e., Day 2, 9, 16) 4 mg of dexamethasone premedication is required to be used prior to second treatment. Missed doses will not be replaced during a cycle. Carfilzomib will be escalated from  $20 \text{ mg/m}^2$  (Cycle 1 Days 1 and 2)

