#### **6.7.4 Renal Function**

Carfilzomib has not been fully characterized in subjects with creatinine clearance  $< 30 \text{ mL/min}$ . It is critical that the subject's renal function is known at the time of dosing. Renal function, serum creatinine, and serum uric acid should be monitored closely during treatment with carfilzomib. Renal function must be monitored closely during treatment with carfilzomib. Serum chemistry values, including creatinine, must be obtained and reviewed prior to each dose of carfilzomib during Cycles 1 and 2. Refer to [Table 6-8](#) for guidance regarding dose reduction in subjects with compromised renal function.

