6. Systolic and diastolic blood pressure, pulse, respiration, temperature approximately 1 hour before dosing.
7. 24 hour urine total protein, urine protein electrophoresis (UPEP), and urine protein immunofixation. For subjects whose disease is being monitored through UPEP, additional post baseline 24-hour urine collections are required as indicated.
8. For subjects whose disease is being monitored through UPEP, additional post baseline 24-hour urine collections are required as indicated.
9. Hemoglobin, hematocrit, WBC with complete differential, RBCs, platelet count. Results must be reviewed before dosing.
10. Cycles 1 and 2 only and subsequent cycles as clinically indicated or per institutional standard of care.
11. Full serum chemistry panel at Screening, Days 1, 8, and 15 of Cycles 1-8, and Day 1 of Cycles 9+: sodium, potassium, chloride, bicarbonate, BUN, creatinine, glucose, uric acid, total protein, albumin, calcium, phosphorus, magnesium, total bilirubin, alkaline phosphatase, ALT, AST, LDH. Results must be reviewed before dosing in Cycles 1 and 2.
12. Abbreviated serum chemistry panel on Days 2, 9, and 16 of Cycles 1 and 2 only or as clinically indicated (e.g., risk factors for tumor lysis syndrome): sodium, potassium, chloride, bicarbonate, BUN, creatinine, glucose, uric acid.
13. Pregnancy tests for females of childbearing potential. A female of childbearing potential (FCBP) is a sexually mature female who: 1) has not had a hysterectomy or bilateral oophorectomy; or 2) has not been naturally post-menopausal for at least 24 consecutive months (i.e., menses within the preceding 24 months).
14. Pregnancy tests must occur within 10-14 days and again within 24 hours prior to prescribing lenalidomide (prescriptions must be filled within 7 days. FCBP with regular or no menstruation must have a pregnancy test weekly for the first 28 days and then every 28 days while on therapy (including breaks in therapy); at discontinuation of lenalidomide and at Day 28 post the last dose of lenalidomide. Females with irregular menstruation must have a pregnancy test weekly for the first 28 days and then every 14 days while on therapy (including breaks in therapy), at discontinuation of lenalidomide and at Day 14 and Day 28 post the last dose of lenalidomide (see Appendix 7 for Risks of Fetal Exposure, Pregnancy Testing Guidelines and Acceptable Birth Control Methods).

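### Section 6.1.2 makes Day 2, 9 and 16 chemistry discretionary in every cycle, against the Cycles 1–2 pre-dose rule in 6.3.1 and 6.7.4, and leaves out the potassium listed in Appendix 8

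*Protocol*

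**What the plan says.** Protocol section 6.1.2 has two chemistry rows. The complete panel is drawn on Days 1, 8 and 15, and its row ends with the rule "Results must be reviewed before dosing in Cycles 1 and 2". The limited panel is drawn on "Days 2, 9, and 16 if clinically indicated" and consists of "Sodium, chloride, bicarbonate, BUN, creatinine, glucose, uric acid". That second row carries no review rule and does not treat Cycles 1 and 2 differently from later cycles.

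Section 6.3.1 places carfilzomib on Days 1, 2, 8, 9, 15 and 16 of Cycles 1–8 and states: "Serum chemistry values, including creatinine, must be obtained and reviewed prior to each dose of carfilzomib during Cycles 1 and 2". Section 6.7.4 repeats that these values "must be obtained and reviewed prior to each dose of carfilzomib during Cycles 1 and 2".

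In Appendix 8, the Serum Chemistry cells for Days 2, 9 and 16 show a bracketed X with footnotes 10 and 12. Footnote 10 reads "Cycles 1 and 2 only and subsequent cycles as clinically indicated or per institutional standard of care". Footnote 12 begins "Abbreviated serum chemistry panel on Days 2, 9, and 16 of Cycles 1 and 2 only or as clinically indicated" and, after giving an example of an indication, lists the panel: "risk factors for tumor lysis syndrome): sodium, potassium, chloride, bicarbonate, BUN, creatinine, glucose, uric acid".

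**The concern.** The same sample is compulsory in 6.3.1 and 6.7.4 and discretionary in 6.1.2. The layout of 6.1.2 makes the relaxation look deliberate: the row for Days 1, 8 and 15 states the Cycles 1–2 review rule, and the row beneath it for Days 2, 9 and 16 does not.

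What is at stake is a safety check. Section 6.7.1 describes a first-dose effect in which creatinine rises on Day 2, and a sample drawn before the Day 1 dose cannot show it. Section 6.4 requires uric acid and creatinine to be back at baseline before carfilzomib doses in Cycles 1 and 2, and Table 6-8 holds carfilzomib when creatinine clearance falls below 30 mL/min. Both rules need a current value. Potassium matters because section 6.7.3 names a rise of at least 30% among the example abnormalities for which the scheduled dose is withheld.

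There is also a monitoring consequence. A missing Day 2 creatinine is a deviation under 6.3.1 and 6.7.4, while 6.1.2 read alone would treat it as compliant.

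**Working it through.** The protocol gives no figure to reproduce here. The check is a comparison of texts, with a count of the doses involved.

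**Timing on Days 2, 9 and 16**

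| Place | Cycles 1–2 | Later cycles | Review before dosing stated? |
|---|---|---|---|
| 6.1.2, limited panel | Only on clinical indication | Only on clinical indication | No |
| 6.3.1 | Required before each carfilzomib dose | Not addressed by this rule | Yes, Cycles 1–2 |
| 6.7.4 | Required before each carfilzomib dose | Not addressed by this rule | Yes, Cycles 1–2 |
| Appendix 8, footnote 10 | Scheduled | Clinical indication or local standard | No |
| Appendix 8, footnote 12 | Scheduled, with a loosely worded alternative | Clinical indication | No |

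Only the 6.1.2 row makes no distinction between Cycles 1–2 and later cycles. Appendix 8 has a smaller gap of its own: footnote 11 (Days 1, 8 and 15) carries the review rule and footnote 12 does not.

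**Panel contents**

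- 6.1.2: sodium, chloride, bicarbonate, BUN, creatinine, glucose and uric acid, which is 7 analytes.
- Footnote 12: the same 7 plus potassium, which is 8.

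The only difference is potassium. It is present in the complete-panel row of the same 6.1.2 table, so damage to the text in conversion is an unlikely cause.

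**Doses exposed to the conflict**, using the section 6.3.1 schedule

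- Carfilzomib doses in Cycles 1–2: 6 × 2 = 12.
- Of these, doses on Days 2, 9 and 16: 3 × 2 = 6, so 6/12 = 50%.
- All planned carfilzomib doses: Cycles 1–8, 6 × 8 = 48; Cycles 9–24, 4 × 16 = 64; total 112. Share: 6/112 = 5.4%.
- Section 4.1 instead gives four carfilzomib days per cycle in Cycles 5–8. On that schedule the total is (6 × 4) + (4 × 4) + 64 = 24 + 16 + 64 = 104, and the share is 6/104 = 5.8%. The Synopsis and Appendix 8 footnote 25 agree with 6.3.1.
- For 45 patients: 6 × 45 = 270 pre-dose samples at most.

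These counts are ceilings. They assume a site follows 6.1.2 and misses 6.3.1, 6.7.4 and Appendix 8.

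**The case against.** The strongest reply is that the rule is secured elsewhere. It stands in the drug-administration section, is repeated under renal function, is reflected in Appendix 8 and is supported by the baseline condition in 6.4. The specific Cycles 1–2 requirement can be read as overriding a general treatment-phase row, and a sample missed against an explicit requirement is a deviation whatever a laxer row says. This lowers the chance of a skipped sample, but it does not remove the conflict. The protocol has no rule of precedence between sections, section 6 offers Appendix 8 as an overview, and 6.1.2 is the procedures table that a coordinator can be expected to work from.

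It can also be said that Appendix 8 is not squarely on the side of 6.3.1, given the bracketed X, the alternative wording in footnote 12 and the absence of a review rule there. That is fair. Even so, footnote 10 ties the discretion to later cycles, and 6.3.1 and 6.7.4 are unconditional.

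On potassium, the list in 6.7.3 is one of examples. It also includes phosphate, calcium and LDH, which neither limited panel contains, so the limited panel was evidently not built to cover that list. This stands as a limit on the weight of the omission. What remains is a plain disagreement between two versions of the same panel.

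The reasons to expect little harm also stand. Full panels are drawn on Days 1, 8 and 15. Section 1.5.2.1 links the BUN and creatinine rises to bolus dosing, whereas this trial infuses over 30 minutes. Section 1.3.4 reports no tumor lysis in more than 350 later patients once prophylaxis was in place. Section 6.3.5 says there will be no new starts. If that means no new patients, the effect from now on is close to zero, and Cycles 1–2 were largely or wholly given under earlier protocol versions that are not at hand. If it means only that no one starts on the subcutaneous form, that comfort falls away.

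**Conclusion.** The concern holds. The 6.1.2 row is wrong as written: followed literally, it omits a pre-dose chemistry check that 6.3.1 and 6.7.4 require, and its panel lacks an analyte that Appendix 8 includes. The conflict covers 6 of the 12 carfilzomib doses in Cycles 1–2, which is 5.4% of planned doses on the 6.3.1 schedule or 5.8% on the 4.1 schedule. The 270-sample figure assumes that all 45 patients are treated under this text at sites that rely on 6.1.2 alone; the actual number is likely to be far smaller.

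Severity is minor. This is an internal inconsistency in safety monitoring, with small practical risk and no bearing on any endpoint, sample size or inference. The bracketed X and the reference in 6.7.3 to a section 7.1.2 that does not exist are clerical and add no weight.

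**What to change.** - **Section 6.1.2, limited chemistry row:** state that on Days 2, 9 and 16 the panel is required, with results reviewed before dosing, in Cycles 1 and 2, and is drawn on clinical indication thereafter. Add potassium.
- **Appendix 8, footnote 12:** require the panel in Cycles 1 and 2 with review before dosing, and leave later cycles to clinical indication. Define the bracketed X or replace it with a plain X.
- **Section 6.7.3:** replace the reference to section 7.1.2 with one to section 6.1.2 (apparently the intended target) and Appendix 8.
- **Optional, not a correction:** add phosphorus, calcium and LDH to the limited panel if it is meant to cover all six example markers in 6.7.3.

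The required changes cost amendment wording and one analyte in 6.1.2 that footnote 12 already lists. They add no visit or blood draw beyond what 6.3.1 and 6.7.4 already require.

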### 6.1.3 End of Treatment Procedures and Long-Term Follow-Up

Patients who discontinue therapy for any reason must have an end of treatment (EOT) visit completed 28 days ( $\pm$  7 days) after the last application of study drug. Following the end of treatment, subjects will be followed for survival and progression for 2 years.

At the EOT visit, the patients will undergo the following assessments:

|                                              |                                                                                                                                                                                                                                |
|----------------------------------------------|--------------------------------------------------------------------------------------------------------------------------------------------------------------------------------------------------------------------------------|
| Pregnancy Test (if applicable)        | FCBP pregnancy testing required at treatment discontinuation and at 28 days following treatment discontinuation. If menstrual cycles are irregular, additional testing 14-days following treatment discontinuation is required |
| Physical Examination and Vital Signs  | 
 
• Body weight
 
• Blood pressure, pulse, temperature
 
• Physical examination
 
• Pulse oximetry to investigator discretion
 
                             |
| Hematology                            | Hemoglobin, hematocrit, WBC count, WBC differential, red blood cell count, platelets. WBC differential may be automated or manual as per institutional standards.                                                              |
| Clinical Chemistry                    | Sodium, potassium, chloride, bicarbonate, BUN, creatinine, glucose, uric acid, total protein, albumin, calcium, phosphorus, magnesium, total bilirubin, alkaline phosphatase, ALT, AST, LDH.                                   |
| Myeloma Disease Assessment–Laboratory | M-protein determination: 
 
• Serum protein electrophoresis and immunofixation
 
                                                                                                  |

|                                    |                                                                                                                                                                                                                                                                                                                                                                 |
|------------------------------------|-----------------------------------------------------------------------------------------------------------------------------------------------------------------------------------------------------------------------------------------------------------------------------------------------------------------------------------------------------------------|
|                                    | 
 
• Urine protein electrophoresis and immunofixation
 
• Serum free light chains and Hevylite test
 
• Serum quantitative immunoglobulins (Igs)
 
                                                                                                                                                   |
| Bone Marrow Aspirate/Biopsy | All BM aspirates are SOC. Quantify percent myeloma cell involvement, and obtain bone marrow aspirate for MRD analysis by NGS. This is required at end of treatment, yearly after EOT up to 2 years, and confirmation of CR. For subjects who sign consent for correlative samples, an additional aspirate sample should be collected at the time of the SOC BMA |
| CT-PET                      | A CT-PET must be performed to confirm MRD-negative disease per standard of care, at every time-point when MRD is checked                                                                                                                                                                                                                                        |
| Neurotoxicity Assessment    | Including Neurotoxicity Questionnaire ( Appendix 5 )                                                                                                                                                                                                                                                                                            |
| QOL Assessment              | Patient reported survey ( Appendix 6 )                                                                                                                                                                                                                                                                                                          |
| Adverse Events              | Record through 30-days after last treatment. All SAEs considered related to treatment must be followed until resolution.                                                                                                                                                                                                                                        |

